## Abstract

**Background:**

Between 40,000 and 80,000 pregnant women die annually from pre-eclampsia and eclampsia. Although magnesium sulphate and anti-hypertensive therapies can reduce the morbidity and mortality associated with pre-eclampsia, the only cure comes with delivery. Prompt delivery of the baby, preferably by vaginal route, is vital in order to achieve good maternal and neonatal outcomes. Induction of labour is therefore a critical intervention in order to prevent morbidity to both mother and baby. Two low cost interventions – oral misoprostol tablets and transcervical Foley catheterization – are already used by some in low resource settings, but their relative risks and benefits are not known. The trial will compare the risks, benefits, and trade-offs in efficacy, safety, acceptability and cost of misoprostol and Foley catheter for induction in women with preeclampsia or uncontrolled hypertension.

**Methods/Design:**

A total of 602 women with an ongoing pregnancy with a live fetus requiring delivery because of pre-eclampsia or uncontrolled hypertension will be randomly assigned to labor induction with a transcervical Foley catheter or oral misoprostol 25 micrograms. Women will be recruited at two hospitals in Nagpur, India. The misoprostol group will receive oral misoprostol 25 microgram every 2 hours for a maximum of 12 doses or until active labor commences. The Foley group will undergo induction using a Foley catheter (silicone, size 18 F with 30 ml balloon) which will remain until active labor starts, the Foley catheter falls out, or 12 hours have elapsed. The primary outcome will be the attainment of vaginal delivery within 24 hours. Providers administering the treatment and those assessing the outcomes will not be blinded to group assignment.

**Trial registration:**

NCT01801410 (ClinicalTrials.gov).

## Background

Between 40,000 and 80,000 pregnant women die annually from pre-eclampsia and eclampsia [1]. Magnesium sulphate and anti-hypertensive therapies can reduce the morbidity and mortality associated with pre-eclampsia [2, 3]. The only cure, however, comes with delivery. Prompt delivery of the baby, preferably by vaginal route, is vital in order to achieve good maternal and neonatal outcomes. Induction of labour is therefore a critical intervention in order to prevent morbidity and mortality to both mother and baby. Two low cost interventions – oral misoprostol tablets and transcervical Foley catheterization – are already used by some in low resource settings, but their relative risks and benefits are not known. These interventions could optimize the care pathway for women needing induction of labour. This is especially important in low resource settings where improvement is most needed and the potential to reduce the maternal and neonatal mortality and morbidity is the greatest. The ideal induction agent would result in a relatively short induction to delivery interval without risk to fetus and with low rates of emergency caesarean section. The induction to delivery interval is especially important in pre-eclampsia and eclampsia where the condition may deteriorate rapidly.

Misoprostol, the orally active and heat stable prostaglandin E1 analogue, has been used for labour induction for nearly 20 years. Following years of debate about appropriate dosage, it appears that the use of oral misoprostol 25 microgram is optimal [4, 5]. A systematic review of low dose oral misoprostol included two trials in which the 25 microgram dose of oral and vaginal misoprostol were compared. It found that “women using oral misoprostol were significantly less likely to experience uterine hyperstimulation with fetal heart rate changes (2% compared with 13%; RR 0.19, 95% CI 0.08-0.46), but there were no significant differences in other outcomes [6]”. The Cochrane review concluded that “Given that safety is the primary concern, the oral regimens are recommended over vaginal regimens. This is especially important in situations where the risk of ascending infection is high and the lack of staff means that women cannot be intensely monitored [4]”. Oral misoprostol is very effective but still has a hyperstimulation rate of 6% [6], potentially causing hypoxic damage to the fetus. The risk of hypoxic damage is increased in pre-eclampsia, where babies may be born prematurely or affected by intrauterine growth restriction. In low resource settings, where access to intrapartum fetal monitoring may be limited, avoidance of hyperstimulation, which may go undetected, is critical.

Alternative low cost methods have been sought that can induce labour with potentially less risk to the fetus. Such an agent may be the Foley catheter. Although usually used for bladder drainage, these catheters can be inserted into the cervix and held there by inflating the balloon. The catheter is then placed on gentle traction by strapping it to the mother’s thigh and left for 12 hours or until it falls out through the cervical os. Induction with the Foley balloon catheter appears to be as effective as current standard methods, but with lower rates of uterine hyperstimulation and better fetal outcomes [7, 8]. However, the majority of the studies (22/30) were conducted in Western settings. Little is known about the rates and risks of infection in low resource settings.

Low-dose misoprostol appears to be an effective alternative for labor induction although inductions with prostaglandins, including misoprostol, are sometimes associated with uterine hyperstimulation and consequent fetal hypoxia. The Foley balloon induction method may have considerable safety benefits for the fetus, although there is conflicting evidence as to its effect on the speed of induction. Both methods are promising, but the relative risks and benefits of the two methods for labor induction among women with pre-eclampsia in low resource settings has yet to be established in a large, randomized trial. We will conduct a multicentre randomized trial comparing misoprostol treatment with Foley balloon induction for labor induction in women with preeclampsia or uncontrolled hypertension. This study will identify the risk, benefits and trade-offs in efficacy, safety, acceptability and cost of these two low cost induction methods.

## Methods

This pragmatic, open-label, randomised control trial will enroll patients seeking care for preeclampsia at Government Medical College and Daga Women’s Hospital, Nagpur. Women with an ongoing pregnancy with a live fetus in whom the decision has been made to induce vaginal delivery because of preeclampsia or uncontrolled hypertension will be included. Women will be excluded if they are less than 18 years old; have previously undergone a caesarean section; present with a multiple pregnancy, ruptured membranes, or chorioamnionitis; or report a history of allergy to misoprostol. All subjects will provide written and oral informed consent and have the informed consent process video recorded as required by Indian regulations. This protocol was approved by the Liverpool School of Tropical Medicine Research Ethics Committee (Approval number 12.26) and the Ethics Committee at Government Medical College, Nagpur and will be conducted in compliance with the Helsinki Declaration.

### Randomisation

At enrolment, the medical history will be assessed and a physical exam will be performed (Figure 1). Women will be randomised independently using a computerised random number generator; the randomisation will be stratified by centre using a randomly determined block size. The group assignment will be indicated in a card sealed in sequentially numbered opaque envelopes. The group assignment will be revealed immediately prior to the start of the induction. The participants, providers, and those assessing outcomes will not be blinded to the group assignment.

**Figure 1 Fig1:**
[figure not shown]
**Consort flow diagram.**

Women in the mechanical group will undergo induction using a transcervical Foley catheter (silicone, size 18 F with 30 ml balloon) which will remain in place until active labour starts, the Foley catheter falls out, or 12 hours have elapsed. If the Foley catheter falls out within 12 hours, membranes will be ruptured and/or oxytocin infusion started. If the Foley catheter does not fall out within 12 hours, it will be removed at 12 hours and oxytocin commenced with an artificial rupture of membranes when possible. If labour has still not commenced after 24 hours, the woman will be deemed to have a ’failed induction’ and the decision on further management will be made by the clinical team. Their choice of method could include the use of misoprostol, repeat Foley catheter, dinoprostone, caesarean section or delay as deemed appropriate.

Women in the misoprostol group will be induced using oral misoprostol tablets (25 micrograms, Cipla Ltd, Mumbai) every 2 hours for a maximum of 12 doses or until active labour commences. In primigravid women, if contractions have not commenced after 2 doses, the dosage may be increased to 50 micrograms every 2 hours. Once in labour (regular painful contractions with a cervical dilatation of at least 4 cm) no more misoprostol will be used and artificial membrane rupture and/or oxytocin infusion will be used as clinically indicated. If labour has still not commenced after 24 hours, the woman will be deemed to have a ‘failed induction’ and the decision on further management will be made by the clinical team. Their choice of method could include the use of misoprostol, repeat Foley catheter, dinoprostone, caesarean section or delay as deemed appropriate.

During the labor induction, women will be monitored by research clinicians every two hours. The use of any additional medications, cervical dilation and Bishop score will be recorded, as appropriate.

Women will be asked to assess their expectations prior to the induction process. Then, within 48 hours of delivery and prior to discharge, women will be interviewed by study staff using a short questionnaire. The questionnaire will assess their opinions about their experience and issues surrounding the induction (including time to induction), their satisfaction with the actual labour, and their perspectives on the two medical technologies. Women will be asked to rate their overall experience on a categorical five-point scale from ‘very unsatisfied’ to ‘very satisfied’ and compare this to their actual experience, with a focus on what they would like to change in any future induction. Care providers’ (nurses and doctors) opinions will also be collected in a separate provider survey (or focus group discussion where appropriate) after the conclusion of the trial.

Participants with severe pre-eclampsia will receive magnesium sulfate and anti-hypertensives as per local protocols.

### Study outcomes

The primary outcome will be the attainment of vaginal delivery within 24 hours. Vaginal delivery within 24 hours is the standard primary outcome suggested in the Cochrane Collaboration induction of labour generic protocol [5, 6]. It combines an acceptable time period for the induction process as well as the combined fetal and maternal safety outcome of need for caesarean section. Caesarean section also poses a serious risk to maternal health in the context of the setting and disease.

Secondary outcomes will assess the success of the induction process, neonatal morbidity and mortality, and maternal mortality and morbidity. Measures of efficacy of the induction process will include the induction to delivery interval (in vaginal deliveries, caesarean sections and all deliveries), the proportion of women in each group with vaginal deliveries within 12 hours, with cervix unchanged at 12 and 24 hours, and with a need for oxytocin augmentation. Measures of maternal complications will include uterine tachysystole (defined as over 5 contractions in 10 minutes), uterine hypertonus (defined as a single contraction lasting over 2 minutes), caesarean section, uterine rupture, instrumental vaginal delivery, severe hypertension and HELLP Syndrome, maternal vomiting, maternal diarrhoea, fever, antibiotic use, and postpartum haemorrhage. Data on the following fetal-neonatal complications will also be collected: meconium-stained liquor, Apgar score less than seven at five minutes, neonatal intensive care unit admission, seizures, birth asphyxia, and stillbirth.

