### Proposed analyses

Logistic, Poisson and negative binomial regression models will be used as appropriate to estimate effect size (difference in vaginal delivery rates) with 95% confidence intervals; adjustments will be made for important confounding variables and covariates. The primary analysis will be done according to intention to treat. If indicated, a secondary, per protocol analysis will be performed. Similar regression models will be used to compare the two study groups with respect to other important (secondary) variables. Subgroup analyses will be parity (nulliparous or not), site of delivery, Bishop score (≥6 or less), and perceived fetal viability (determined by the provider at enrolment).

We will conduct an economic evaluation to assess patterns and levels of resource utilisation associated with the two induction techniques. This analysis will enable any variations in resource use between the two treatment groups to be identified, measured and valued and facilitate the linking of patterns/costs of resource use to maternal and child health outcomes and other agreed measures of ‘effectiveness’ and ‘success’.

An interim analysis will be conducted after one year of recruitment, or when data are available from the first 300 women. The data will be reviewed by an independent Data Monitoring Committee. Further interim analyses are not planned, but may be requested by the Data Monitoring Committee. No interim analyses for effectiveness or futility are planned.

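### Comparing arms on the induction-to-delivery interval within vaginal deliveries and within caesareans conditions on a post-randomisation outcome; compare speed in all randomised women instead

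*Protocol article*

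**What the plan says.** Under Study outcomes, the first measure of efficacy of the induction process is the "induction to delivery interval (in vaginal deliveries, caesarean sections and all deliveries"). This defines three analysis sets: women who deliver vaginally, women delivered by caesarean, and all women.

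Under Proposed analyses, the plan states: "Similar regression models will be used to compare the two study groups with respect to other important (secondary) variables". Read together, the two sections commit to comparing the arms on the interval in each of the three sets.

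The article also makes mode of delivery an outcome. Caesarean section is in the list of maternal complications ("uterine hypertonus (defined as a single contraction lasting over 2 minutes), caesarean section, uterine rupture, instrumental vaginal delivery"), and the rationale for the primary outcome says: "It combines an acceptable time period for the induction process as well as the combined fetal and maternal safety outcome of need for caesarean section". On masking, Randomisation states: "The participants, providers, and those assessing outcomes will not be blinded to the group assignment".

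The interval is not a minor item for this trial. The Background says: "The induction to delivery interval is especially important in pre-eclampsia and eclampsia where the condition may deteriorate rapidly".

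**The concern.** Randomisation makes the two arms comparable as wholes. It does not make the women who deliver vaginally in one arm comparable with those who deliver vaginally in the other, because who ends up in that set depends on what happened after allocation. A caesarean done during a slow labour removes that labour from the vaginal-delivery set, so the women left behind are the quicker ones. The more often or the earlier this happens in an arm, the shorter its vaginal-only interval. The caesarean-only interval likewise depends on when, and for whom, the decision to operate was made. Analysis by intention to treat keeps women in their allocated arm but does not restore comparability inside a set defined by an outcome.

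At stake is a wrong reading of which method works faster. An arm could show a shorter vaginal-only interval and at the same time a lower proportion of vaginal deliveries within 24 hours. A reader who took the interval as evidence of speed would then draw a conclusion opposite to the primary outcome.

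**Working it through.** **The plan's own figure.** There is none to reproduce. The article states no expected interval, no caesarean rate for either arm, and no sample size for this outcome. Everything below is an illustration with assumed inputs.

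**Step 1: what the sets condition on.** Interval in vaginal deliveries: restricted to women without caesarean. Interval in caesareans: restricted to women with caesarean. Caesarean occurs after allocation, is a listed outcome, and is decided by staff who know the arm. So two of the three sets are defined by something that treatment can affect. The all-deliveries set is not.

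**Step 2: closed-form illustration (assumed constant hazards).** Vaginal-delivery hazard v = 0.03/h in both arms; caesarean hazard c = 0.01/h in arm A and 0.02/h in arm B.

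- Proportion with caesarean = c/(v+c): A 0.01/0.04 = 25%; B 0.02/0.05 = 40%.
- Mean interval among vaginal deliveries = 1/(v+c): A 1/0.04 = 25.0 h; B 1/0.05 = 20.0 h.
- Vaginal delivery within 24 h = v/(v+c) × (1 − exp(−24(v+c))): A 0.75 × (1 − e^−0.96) = 46.3%; B 0.60 × (1 − e^−1.2) = 41.9%.

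Arm B looks 5.0 h faster among vaginal deliveries yet has fewer of them by 24 h. With c = 0.015/h in arm B the mean is 1/0.045 = 22.2 h, a gap of 2.8 h.

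This example has a limit. Under constant hazards, time and mode are independent, so the mean in all deliveries is also 25.0 h against 20.0 h. The 5 h is a real difference in time to delivery by any route. The example shows only that a shorter interval need not mean faster vaginal delivery; it does not isolate an effect of conditioning.

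**Step 3: simulation without constant hazards (assumed).** Each woman has an underlying time to vaginal delivery (lognormal, median 22 h, log-SD 0.6) and an independent underlying time to caesarean (lognormal, log-SD 0.5, median as in the first column). The earlier of the two happens. There are 400,000 simulated women per row; other columns are results.

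| Median caesarean time assumed (h) | Caesarean | Median interval, vaginal (h) | Median, caesarean (h) | Median, all (h) | Vaginal delivery within 24 h |
|---|---|---|---|---|---|
| 60 | 10% | 20.5 | 34.4 | 21.7 | 55% |
| 45 | 18% | 19.4 | 28.4 | 20.9 | 54% |
| 36 | 26% | 18.3 | 24.3 | 19.9 | 52% |
| 30 | 35% | 17.3 | 21.4 | 18.8 | 49% |
| 24 | 46% | 16.0 | 18.3 | 17.1 | 44% |

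The underlying time to vaginal delivery is the same in every row. Between adjacent rows (caesarean rates 8 to 11 points apart) the vaginal-only median differs by 1.0 to 1.3 h; between the first and last rows by 20.5 − 16.0 = 4.5 h. The all-deliveries median moves by 21.7 − 17.1 = 4.6 h, because caesareans do end pregnancies sooner in the lower rows.

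**Step 4: can the order reverse?** Give one arm a truly slower underlying time (median 25 h, caesarean median 24 h) and the other 22 h and 60 h. Caesareans are 52% against 10%, and vaginal delivery within 24 h is 37% against 55%. The vaginal-only median is 17.3 h against 20.5 h, so the slower arm looks faster. This is a deliberately large contrast in caesareans and shows possibility, not likelihood.

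**The case against.** The strongest reply is that the protocol already answers the question of speed in ways that respect randomisation, and that most of what a critic might add does not follow from the text. Much of this stands.

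- **Vaginal delivery by fixed times is already planned in all women.** It is the primary outcome at 24 hours and a secondary outcome at 12 hours, and a caesarean counts as non-success in each. With no anticipated loss to follow-up, these are the cumulative incidence of vaginal delivery at those times.
- **The all-deliveries interval is valid.** A reader might infer that all three versions are biased. The third keeps every randomised woman, and time to delivery by any route is meaningful in a disease that delivery cures. It needs only to be read beside the caesarean rate.
- **No unsuitable model is fixed for the interval.** A reader might infer that binary or count models will be fitted to hours. The article says "Logistic, Poisson and negative binomial regression models will be used as appropriate to estimate effect size (difference in vaginal delivery rates") and then speaks of similar models for secondary variables. That assigns no model to the interval, and the choice is commonly left to an analysis plan, which is not shown.
- **A caesarean for failed induction is not recorded as a fast delivery.** Failed induction is declared only if labour has not commenced after 24 hours, and caesarean is then one option among several: "Their choice of method could include the use of misoprostol, repeat Foley catheter, dinoprostone, caesarean section or delay as deemed appropriate". Only caesareans done earlier for other reasons can shorten the interval below that.
- **No difference in caesarean rates is forecast.** The planning rates concern vaginal delivery within 24 hours and could differ through timing alone.

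What the reply does not remove is the naming of the vaginal-only and caesarean-only sets as efficacy measures to be compared between arms. An unseen analysis plan could choose the model, but no choice of model makes those two sets comparable.

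**Conclusion.** The point holds for two of the three planned interval comparisons. Those within vaginal deliveries and within caesareans are made in sets defined by a post-randomisation outcome, in an open-label trial, and should not carry an efficacy claim. The all-deliveries comparison stands.

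The size is unknown. In the simulation a caesarean difference of 8 to 11 points goes with about 1 h in the vaginal-only median, and 10% against 46% with 4.5 h. These figures rest on assumed lognormal times, independence of the two times, and assumed caesarean timing. Other assumptions would change the size and could change the direction, so the claim is that an arm with more or earlier caesareans can look faster, not that it will. The 5 h in the constant-hazards example should not be quoted as the bias, for the reason given there.

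The issue concerns one secondary outcome. A reader might infer that it weakens the primary comparison or the sample size of 602; it touches neither.

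**What to change.** 1. Report the interval within vaginal deliveries and within caesareans as medians by arm, labelled descriptive, with no between-arm test and no efficacy claim.
2. Compare speed in all randomised women, from a start time defined identically in both arms, as time to vaginal delivery with caesarean as a competing event. Show cumulative incidence curves by arm; read at 12 h and 24 h they should agree with the proportions already planned.
3. Also compare time to delivery by any route in all randomised women, presented next to the caesarean rate in each arm.

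The cost is a few sentences in the analysis plan and slightly more programming. The inputs are times and modes of delivery, which the listed outcomes already require, so no new data collection is needed.

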### Statistical analysis

The primary outcome will be vaginal birth within 24 hours. The rate of vaginal delivery within 24 hours in the Foley catheter group is estimated at 41%. This rate is taken from the study by Pennell [9] which compared a Foley catheter for 12 hours with vaginal misoprostol and found a rate of vaginal delivery in the Foley group within 24 hours of 53/110 (48%) [9]. Only two other studies were identified that used the same induction protocol and outcomes as planned for this study (i.e. a 12 hour Foley under traction and an outcome of vaginal birth within 24 hours). In Yuen [10] the vaginal delivery rate within 24 hours was 15/36 (42%), and in Owolabi [11] the rate was 17/60 (28%) [10, 11]. The combined rate from these 3 studies is 85/206 (41%).

In the Cochrane review of oral misoprostol 25 microgram versus PGE2 which included 5 trials, the vaginal delivery rate within 24 hours in the 25 microgram oral misoprostol group was 654/1089 (60%) [4]. The vaginal delivery rate in this study is likely to be increased because there will be little intrapartum fetal monitoring, a factor that is known to increase caesarean section rates. However, more women will be having labor induced preterm (with more unfavourable Bishop scores) – a factor that also increases caesarean section rates. Our estimated rate of vaginal delivery within 24 hours in the misoprostol group is therefore 60%.

The null hypothesis is that there is no difference in the rate of vaginal delivery within 24 hours in those induced with misoprostol and those induced with a Foley catheter. This hypothesis will be rejected if there is a 33% difference in the outcomes with the two methods. To detect an absolute increase from 41% to 55% with 90% power (two-sided α = 0.05) will require a sample of 602 women. If the vaginal birth rate in the Foley group is higher, then the study will have more power. As stated previously, we do not anticipate any loss to follow-up.

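### The stated rejection rule (a 33% difference) is not the two-sided 5% test the trial was sized for; applied literally it has about 50% power at the design effect instead of 90%

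*Protocol article*

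**What the plan says.** All the relevant text is in one paragraph of the Statistical analysis section of the protocol article.

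- Null hypothesis: "The null hypothesis is that there is no difference in the rate of vaginal delivery within 24 hours" between the two induction methods.
- Rejection rule, in the sentence that follows: "This hypothesis will be rejected if there is a 33% difference in the outcomes with the two methods".
- Design, in the sentence after that: "To detect an absolute increase from 41% to 55% with 90% power", at a two-sided α of 0.05, which "will require a sample of 602 women".

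Earlier in the section the Foley rate is put at 41% (85/206 pooled over three studies) and the expected misoprostol rate at 60%. The Proposed analyses section plans regression models with 95% confidence intervals and an intention-to-treat primary analysis. It does not say which p-value or interval decides the primary comparison. The article does not say whether the 33% is relative or absolute, or that it is only the effect assumed for sizing.

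**The concern.** A design alternative is the true effect at which a test should have the stated power. A rejection threshold is the observed result at which the null is abandoned. The threshold has to lie well below the alternative, otherwise 90% power is impossible. If the two coincide, the observed effect falls short of the threshold about half the time even when the assumed effect is real.

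The article's only explicit statement of when the null is rejected puts the design alternative in the place of the threshold. Followed literally, a benefit that is significant at 5% would be reported as no difference, and neither the 90% power nor the 5% type I error in the next sentence would be true. The trial is also open-label. Two competing rules in the protocol leave room to choose between them after the results are known.

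**Working it through.** **Inputs.** From the Statistical analysis section: Foley rate 41%, design misoprostol rate 55%, expected misoprostol rate 60%, power 90%, two-sided α 0.05, total 602, no loss to follow-up. Assumption: 1:1 allocation, so 301 per arm, because no ratio is stated.

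**1. Reproducing 602.** A 33% relative increase on 41% is 0.41 × 1.33 = 0.545, which rounds to 55%. The pooled-variance formula per arm is

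n = [z₀.₉₇₅ √(2p̄(1−p̄)) + z₀.₉₀ √(p₁(1−p₁) + p₂(1−p₂))]² / (p₂−p₁)²

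With p₁ = 0.41, p₂ = 0.545, p̄ = 0.4775:

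- n = [1.960 × 0.7064 + 1.282 × 0.6999]² / 0.135² ≈ 285.6, so 286.
- Continuity correction: n′ = (n/4)[1 + √(1 + 4/(n × 0.135))]² ≈ 300.2, so 301 per arm and **602 in total**.

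Taken literally, 41% vs 55% gives 532 without and 560 with the correction. So 33% is the relative effect behind the sample size. (An exact 14-point rise would be 14/41 = 34%.)

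**2. Where the 5% test rejects.** Near the design rates the critical difference is 1.96 × √(2 × 0.48 × 0.52/301) = 0.080, or 8.0 points, which is 0.080/0.41 = 19% relative. The 33% rule needs 0.33 × 41 = 13.5 points.

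In counts, with 123/301 (40.9%) on Foley:

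- The 5% test rejects from 147/301 (48.8%): difference 8.0 points, ratio 147/123 = 1.20.
- The 33% rule needs 1.33 × 123 = 163.6, so 164/301 (54.5%), where p is about 0.0008.
- Every result from 147 to 163 is significant at 5% but not rejected under the written rule. An example is 150/301 (49.8%), with p = 0.027.

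**3. Operating characteristics.** These come from exact enumeration of two Binomial(301, p) arms. The 33% rule is read as an observed ratio of at least 1.33 or at most 1/1.33. The comparator is the pooled two-sided 5% test.

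| True rates (Foley vs misoprostol) | 33% rule | 5% test |
|---|---|---|
| 41% vs 54.5% | 50.3% | 91.4% |
| 41% vs 55% | 54.3% | 93.0% |
| 41% vs 60% (protocol's expected rates) | 87.8% | 99.7% |
| 48% vs 60% (Foley rate from the 53/110 study alone) | 21.1% | 84.5% |
| 41% in both arms (type I error) | 0.41% | 5.1% |
| 48% in both arms (type I error) | 0.09% | 4.9% |

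**4. Other readings of the 33%.** If the threshold is the 14-point absolute difference, power at 41% vs 55% is 49%. If it is 33 percentage points, power is below 0.0001% at 41% vs 55% and about 0.02% at 41% vs 60%.

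**The case against.** The strongest reply is that the sentence is a misworded design effect that nobody would apply. It sits in the sample-size paragraph, the next sentence gives a conventional α and power, 33% relative reproduces 602, and the Proposed analyses section plans 95% confidence intervals. The formal test may also be set out in a full protocol or analysis plan that is not shown. On this view the trial is properly sized, and the 50% figure is a consequence of setting the threshold equal to the true effect. At the protocol's own expected 60% the literal rule has 88% power, and its type I error errs on the conservative side.

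Much of this stands. The intent was very probably the design effect, the 602 is not too small for a 5% test, and the literal rule adds no false-positive risk. The 33-percentage-point reading is implausible, because 41 + 33 = 74% appears nowhere in the article.

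It does not remove the problem. The article states a rejection rule and contradicts it in the next sentence, which is an error rather than an omission. Planned confidence intervals do not override a stated rule. An analysis plan using p < 0.05 would be in conflict with the published protocol. The 50% to 54% applies at the design alternative, which is exactly where the article claims 90%.

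**Conclusion.** The concern holds. As written, the rejection rule is incompatible with the two-sided 5% test and the 90% power stated beside it. At the design effect the literal rule has 50% to 54% power, against 91% to 93% for the 5% test, and a type I error of about 0.4%. With 123/301 on Foley, misoprostol results from 147 to 163/301 would be significant at 5% and still not lead to rejection.

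These figures assume 1:1 allocation and a relative reading of the 33%. The power loss shrinks as the true effect grows, to 88% against 99.7% at 41% vs 60%. It occurs only if the sentence is followed literally. The fault is in the wording of the decision rule for the primary outcome, not in the sample size.

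**What to change.** Replace the rejection sentence with wording such as:

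> The null hypothesis will be rejected if the two-sided p-value of the primary intention-to-treat comparison is below 0.05; the matching 95% confidence interval will be reported. A relative increase of 33% over the Foley rate (41% to 54.5%) is the effect the trial is powered to detect, not the threshold for rejection.

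Use the same rule in the analysis plan. Writing 54.5% in place of the rounded 55%, and naming the continuity correction, would let a reader reproduce the 602.

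The cost is one sentence of protocol wording. Sample size, data collection and trial conduct do not change. The correction should be dated before any comparison of outcomes by arm is seen, because the treatment is not blinded.
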